#### Control group

In the control group, patients will receive the usual standard of care provided at AKUH for stroke/CAD patients. This primarily consists of regular follow-up visits (frequency as per patient needs) with their stroke neurologist or cardiologist.

For index stroke patients, the standard schedule for clinic visits after an uncomplicated recovery is 2 weeks, 1 month, 3 months and 6 months. On each clinic visit, a detailed neurological examination is performed, stroke risk factors are assessed and concerns and queries are addressed. Each patient is provided with a telephone number that can be used to reach the stroke team in case of an emergency.

For index CAD patients especially those after a MI the standard outpatient visit schedule after an uncomplicated recovery is at 1 week, 1 month, 3 months and 6 months. On each clinic visit, a detailed cardiovascular examination is performed and CAD risk factors are assessed.

In both clinics, patients will be provided with a helpline number to which they can send a message if they have any queries regarding their illness or medications. These queries will be answered within the next 24 hours by a physician.

In the control group, during clinics, patients are counseled regarding beneficial lifestyle practices and the significance of compliance with medication regimens. They are also are offered reading materials about their disease in English or Urdu. None of these activities, however, are extended beyond their clinic visit. Each patient also receives clinic appointment reminders 1–2 days prior via SMS and/or phone as per the center policy. The control group does not receive any SMS for lifestyle management or an IVR system that describes their medication prescription in detail [14].

The reason for choosing this site and control group is due to the standardization of care at this center and its adherence to protocols. This assures that differences observed are due to the intervention itself and does not allow overestimation of effect.

### Technical detail: Talking Rx intervention

The system operates on the following two types of applications, which are integrated to each other:Desktop-based imaging application: this is used for scanning the prescription page, detecting markers of medications, dose and frequency, and then translating it into an XML form which is understandable by the web-based medical record applicationWeb-based medical record application: this is hosted on a web-based server which registers patients, keeps patients’ pharmacy data, translates XML into record form and communicates with other messaging servers through CSV file and HTTP protocols

In addition to the above-mentioned applications, the system has a messaging and voice server. This server is hosted at the service provider and contains an application which stores all audio files in coded form. The application accepts CSV file format from the web-based server and binds specific audio files and messages based on the prescribed medicines with patients’ mobile phone numbers. This server allows the web-based medical record to send SMS to patients through HTTP protocols so that they can call this server from their mobile phones to hear their prescription.

#### Technical flow

The IVR flow of the intervention is as follows:Patient registration: the patient is registered on web-based application with his/her demographics, history and mobile numberAcquisition: after receiving a scanned patient’s prescription on an OMR sheet, a health professional/receptionist/research assistant scans the OMR sheet through a scanner using the web-based application. This web-based application opens a desktop-based application to scan the sheet, convert it into an image and then translate it into XML formatProcessing: upon scanning, the web-based application obtains an XML file and translates it into patient records on the basis of patient registration number. After obtaining all the information, the web application shows the medical drug status of each patient so that the user can change status, i.e., activate and deactivate a drug accordingly. Upon confirmation of the request, the web-based application sends a message to the messaging and voice server which allocates patient-specific drugsMessaging: upon registration or changing of a prescription, a patient will receive SMS from the messaging server along with an IVR short code to call a specific number to hear their prescription, within 4 hoursVoice response: as needed, patients can call the IVR short code at any time and hear their prescription details like frequency, indications, contraindications, side effects, etc.Periodic messaging: based on diseases and drugs, the web-based system sends customized messages to patients through the messaging server periodically. Through this feature, behavior change communication is established to promote positive behavior in patients

### Outcomes: (Additional file 2 − Data Collection Form)

The primary outcome of interest is a change in medication adherence after 3 months of receiving the SMS and being exposed to the Talking Prescription (*Bolta Parcha*). Our secondary outcome is change in health literacy. The findings of the treatment group on these outcomes will be compared to the corresponding findings from the control group to account for the Hawthorne effect.

Medication adherence will be measured at recruitment and after 3 months in both groups using the MMAS. The scale has been used in a similar setting previously and it has been translated and validated in Urdu. The change will be determined by comparing the score on the MMAS before and after the intervention [15].

The instrument consists of eight questions and the response to each question is scored as either 0 (yes) or 1 (no). The maximum score, hence, is 8. A higher score indicates better adherence. A score of less than 2 indicates low adherence.

The secondary outcome measure is assessment of functional health literacy in adults (TOFHLA) which will be assessed at enrollment and then at the follow-up visit after 3 months. This tool has been adapted, modified, and content-validated by a panel of experts, translated and back-translated from English to Urdu, to better represent the Pakistani community and its health system. It consists of two sections: the first section covers questions about the basic instructions for each patient coming to the clinic, and the second section contains three passages comprised of questions about the relevant information every patient visiting the hospital should ideally possess.

Section 1 has a total of 17 questions, where a correct answer merits a score of 1 and an incorrect answer gets a score of 0. First Raw score is obtained after adding responses to each question and this score out of 17 is converted to a weighted score, using a reference table, to a denominator of 50.

Section 2 has a total of 50 questions, where each correct answer earns a score of 1 for the patient and an incorrect answer earns a score of 0. The total score at the end of this section is scored out of 50.

In the end, TOFHLA is evaluated on a total of 100, where health literacy is given a total score ranging between 0 and 59 (inadequate), between 60 and 74 (marginal), and from 75 up to 100 (adequate) [8].

In addition, we will perform sensitivity analyses comparing the correlation between the MMAS and the pill count.

### Study timeline

Prior to each stroke/cardiology clinic visit, potential study participants will be identified from the clinic appointment lists. These patients, along with all other walk-in patients, will be approached by research officers during their visit to assess their eligibility for participation through an eligibility questionnaire. Those found eligible are informed about the study and if willing, will be requested to remain after their appointment for recruitment and providing written, informed consent. If a participant is interested but does not have time, they will be offered information about the study and asked to consider participation in the study at their next clinic visit.

First, counseling is performed by a research officer, in which details of the study, its purpose, objective, procedure and its follow-up visits are explained to the eligible participant. Recruitment will begin with signing of an informed consent and assigning the patient an ID number. Data collection will begin with a detailed interview regarding the demographic and clinical details of the patient including his/her prescription details. The baseline MMAS and TOFHLA scores for each patient will then be assessed. This will be followed by the research staff leaving the room and a senior investigator taking over, at which point the patient will be randomized to either the intervention or the control group by the CTU. The tasks of allocation of intervention and randomization are carried out by the CTU staff (separate from the study staff) and are independent from all studies that are ongoing at the university site.

If the patient is allocated to the intervention arm, the investigator will explain the details of the intervention. The investigator will also demonstrates it by sending one test SMS on his/her cell phone (in English and Urdu both). Any questions pertaining to the use and comprehension of IVR or SMS will be answered at that point.

Patients in the intervention arm will then be provided with a number on which they can dial (free-of-cost) the Talking Prescription. The unblinded investigator will then demonstrate this call to the participant and provide orientation regarding proper use of this IT facility.

If there is a change in patient prescription with respect to any drug or dose by any physician, the patient will be requested to notify this on a helpline number that is provided to them during enrollment. In addition, there is a fortnightly review by a research officer to screen and ensure safety and to draw attention to any prescription change that has not been noticed. This allows the Talking Prescription to be modified so that the patient can then be sent instructions according to the new regimen. The helpline is available round the clock and it could also be reached in the case of any queries. The operator at the helpline is trained to answer and deal with most frequently anticipated questions and queries and is given access to a stroke neurologist and a cardiologist at all times in case of queries beyond the scope of their knowledge. If it is anticipated that the participant will undergo frequent medication changes, associated with, e.g., planned carotid endarterectomy (CEA), CABG, stent, etc., they are not enrolled into the program until their condition is stable.

Following the recruitment visit, the patients will not be required to come back to clinic for any additional visits except the end of the study visit at 3 months. The only exception to this will be the select sub-set which is selected for a pill count, which have a fortnightly review. At the end of the study, patient adherence and health literacy is assessed by the research officer who is unaware of patient allocation. (Fig. 3 − Participant timeline for Talking Rx).

**Fig. 3 Fig3:**
[figure not shown]
Participant timeline. Timeline for Talking Prescriptions (Talking Rx) − participants are followed for 3 months. The intervention arm receives Interactive Voice Recording (IVR) that improves prescription literacy and a short text message service (SMS) that cues medication adherence behavior. The Pill Count Sub-study is at 2-week follow-up

### Duration

The trial will continue until we achieve our sample size of 200 (100 in each arm). Follow-up for each study participant will be 3 months from the day of randomization.

### Sample size

The sample size was calculated to detect a difference of 1 point on the primary outcome measure, MMAS, with a power of 90 % and significance level of 5 % between the two groups. The estimated sample size for the study is 86 participants in each arm. Accounting for a 15 % attrition rate the minimum sample size required for the study is 100 participants per arm, making a total of 200 participants to be randomized. The MMAS categorizes low adherence as a score of <6, medium adherence as a score of 6 to <8, and high adherence as a score of 8 [16]. Any 1-point shift is a clinically important increase in scores. In addition, in a study carried out locally, we have shown the use of IT-based interventions to have effects on this score in these ranges [17, 18].

### Assignment of interventions

Sealed opaque envelopes with patient assignments to either the intervention or the control group will be prepared by the CTU through a computerized block randomization technique in block sizes of 10. This is to ensure similarity between the two groups at all times, permitting interim analysis during the study. Additionally this design block was not discussed with the research team interacting with participant recruitment.

The randomization numbers are sealed in opaque envelopes, marked by ID and kept with the CTU. Even if the envelope was held against bright sunlight, the allocation would remain hidden. After enrollment, obtaining informed consent and completing the baseline measurements, the CTU is informed and randomization of the participant is performed.

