**Fig. 1 Fig1:**
[figure not shown]
Study flow chart. Standardized Consolidated Standards of Reporting Trials (CONSORT) flow for the Talking Prescription (Talking Rx) program

They will be randomized into two parallel groups (intervention group and control group) in a 1:1 ratio via block technique. Both groups will have access to a helpline number to address their queries regarding their illness and medications in addition to receiving the standard of care as per institutional guidelines. In addition, participants in the intervention group will also have access to Interactive Voice Response (IVR)-based informative voice messages tailored to their respective prescriptions. The intervention group will also receive daily tailored text messages regarding dosage and frequency of intake of statins and anti-platelet medications. They would also receive weekly text message reminders to improve medication adherence, lifestyle changes, medication information, risk factors and motivation to improve adherence. These messages are modeled on Social Cognitive Theory and the Health Belief Model and are categorized by Michie’s Taxonomy of Behavioral Change Communication [5, 6].

Patients’ adherence to medications will be assessed using the Morisky Medication Adherence Scale (MMAS) [7]. In a sub-set of patients (20 % of patients in each group), pill count will be performed to assess the correlation between self-reported MMAS and direct pill count. Patient’s health literacy will be measured at baseline and then after 3 months in each group by using Likert’s Scale for Health Intelligence Literacy, Knowledge of Medications, and a modified version of Test of Health Literacy in Adults (TOFHLA) (modified version) [8–10]. The difference in adherence to medication regimen (and health literacy) before and after the intervention will be compared between the two groups to determine the effectiveness of our intervention.

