### Participants

Participants attending neurology and cardiology clinics at AKUH are recruited as study participants based on the following criteria:

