### Statistical methods

Analysis will be performed using the intention-to-treat principle: an interim analysis after 25 % of the sample has been reached and final analysis after data has been collected from all study participants. Since this is an IT-based intervention, we plan to do an interim analysis to assess technical compliance to intervention, any unexpected side effects like participant fatigue and drop out. We do not expect any serious safety issues to arise as this study only concerns reception of educational intervention.

The use of the intention-to-treat principle for analysis means that all patients will be analyzed in the treatment arm to which they were randomized. Analysis will be performed after the completion of follow-up of all study participants. Protocol deviations and exclusions (with reasons, will be reported for each arm of the trial). Estimates of intervention effects will be presented with 95 % confidence intervals. A two-tailed *P* value of ≤0.05 will be considered statistically significant for the outcome measures.

For descriptive analysis, mean with standard deviation or median with interquartile range will be reported for continuous data. For categorical data, frequency with percentages will be calculated.

The primary outcome analysis will be based on improvement in medication adherence level, assessed by the change in MMAS score at 3 months of follow-up. To report the difference between the mean scores of intervention group and control arm, Student’s *t* test or the Mann-Whitney *U* test will be performed.

To evaluate the secondary outcome, change in functional health literacy assessed by TOFHLA, the difference of proportion between the two arms will be calculated either by Pearson’s chi-square test or Fisher’s exact test.

To evaluate the correlation between adherence to medications and pill counts either Pearson’s correlation or the Spearman rank correlation test will be applied and coefficients will be calculated to report the strength of correlation.

All analysis will be performed on Stata version13.

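### Blocks of 10 equalise the numbers per arm, not the stroke/CAD mix: correct the stated claim and put index disease into the analysis models

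*Protocol article*

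**What the plan says.** Assignment of interventions describes envelopes prepared by the Clinical Trials Unit (CTU) using a "computerized block randomization technique in block sizes of 10". The next sentence gives the reason: "This is to ensure similarity between the two groups at all times, permitting interim analysis during the study". Design overview describes the allocation as "in a 1:1 ratio via block technique". Neither section, nor the abstract, names a stratification factor.

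The population is mixed. Under Participants: "Participants attending neurology and cardiology clinics at AKUH are recruited as study participants". The inclusion criteria accept a history of stroke or of CAD, so this factor is known before randomization.

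Under Statistical methods, the primary outcome is the change in MMAS at 3 months. "To report the difference between the mean scores of intervention group and control arm", the article names Student's t test or the Mann-Whitney U test. For TOFHLA it names Pearson's chi-square or Fisher's exact test on proportions. None of the four takes a covariate.

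**The concern.** The article credits the design with a property that it lacks. Permuted blocks on one list constrain how many patients have gone to each arm. They place no constraint on who those patients are. Index disease is the most visible characteristic left unconstrained, because the trial combines two diagnoses recruited through two specialties.

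Two modest things are at stake. First, a reader may take similarity of the arms as guaranteed when it is only expected on average. Second, if stroke and CAD patients differ in how their adherence or health literacy changes over 3 months, an unadjusted comparison carries any chance imbalance into the observed estimate and leaves the between-disease variation in the error term. A baseline factor already recorded at eligibility can remove both at almost no cost.

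**Working it through.** **Inputs from the article.** Blocks of 10, 1:1; 200 randomized, 100 per arm; 86 per arm needed before 15% attrition; target difference 1 MMAS point; power 90%; two-sided 5%; interim at 25% of the sample, which is 50 patients.

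**Assumptions.** The SD of the MMAS outcome, the stroke/CAD split and the stroke-CAD gap in MMAS change are not given. I take 50% stroke (30% as an alternative) and a gap of 1 point (range 0.5 to 1.5). The SD comes from the next step.

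**1. The plan's own sample size.** n per arm = 2(1.960 + 1.282)² SD²/1² = 21.01 SD². Setting n = 86 gives SD = 2.02. With SD 2 the normal formula gives 85 and the t-based calculation gives 86, so the stated figure is reproduced with an SD of about 2.

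**2. What blocks of 10 guarantee.** Each block holds 5 and 5. The arms are equal at 10, 20, …, 50, …, 200. Inside an open block they can be up to 5 apart, for example after 45 patients. So even equality of numbers does not hold at every moment.

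**3. Chance imbalance in stroke share.** SD of the difference = √[p(1 − p)(1/n + 1/n)].

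| Per arm | Stroke share | SD (points) | P(gap ≥ 10 points) | P(gap ≥ 20 points) |
|---|---|---|---|---|
| 100 | 50% | 7.1 | 0.179 | 0.006 |
| 100 | 30% | 6.5 | 0.142 | 0.003 |
| 25 | 50% | 14.1 | 0.480 | 0.203 |
| 25 | 30% | 13.0 | 0.440 | 0.164 |

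The probabilities are exact, for two independent binomials. Simulating 20,000 sequences of actual blocks of 10 gave nearly the same values (0.181 and 0.141 for a 10-point gap at 100 per arm). At 50% stroke, 95% of trials fall within 14 points at 100 per arm.

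**4. Shift in the estimate.** Shift = imbalance × gap. For a 10-point imbalance: 0.10 × 0.5 = 0.05, 0.10 × 1 = 0.10 and 0.10 × 1.5 = 0.15 MMAS point. The standard error with SD 2 and 86 per arm is 2√(2/86) = 0.305, so these shifts are about 0.16, 0.33 and 0.49 of one standard error.

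**5. Validity of the unadjusted test.** In 6,000 simulated null trials with 172 completers, the unadjusted type I error was 0.052 (gap 0.5) and 0.055 (gap 1). The Monte Carlo standard error is √(0.05 × 0.95/6,000) = 0.003, so both agree with 5%.

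**6. Gain from adjusting for disease.** For a 50/50 factor with gap δ, the share of variance explained is (δ²/4)/SD². The residual SD is 2√(1 − share).

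| Gap δ | Variance explained | Residual SD | Power, 86 per arm |
|---|---|---|---|
| none | 0 | 2.00 | 0.903 |
| 0.5 | 1.6% | 1.98 | 0.908 |
| 1.0 | 6.3% | 1.94 | 0.920 |
| 1.5 | 14.1% | 1.85 | 0.940 |

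**7. Effect of separate lists.** With blocks of 10 run within each disease (50% stroke), the 95th percentile of the gap at 200 patients falls from 14 to 2 points.

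**The case against.** The strongest reply is that nothing here threatens the trial's validity. Chance imbalance in an unstratified randomized trial is already allowed for by the confidence interval, and not stratifying 200 patients is a legitimate choice. The outcome is change in MMAS, so a stable difference in adherence level between the diseases largely cancels. Nothing in the article shows that disease predicts change. The word similarity may also have been meant as similarity of numbers. Most of this stands and limits the size of the point. The last part does not rescue the sentence, because numbers too can differ inside an open block.

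A second reply is that covariates are commonly left to an analysis plan, which is not shown here. That would answer a complaint about silence. But the article names its tests, and those tests take no covariate; a fuller plan that adjusts would have to be reconciled with them.

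Two stronger readings are tempting and are not supported:

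- A reader might infer that the diseases receive different follow-up care during the trial. Under Control group, "For index CAD patients especially those after a MI the standard outpatient visit schedule after an uncomplicated recovery is at 1 week", against a first stroke visit at 2 weeks. The later visits (1, 3 and 6 months) are the same for both, and eligibility requires more than 1 month since the last episode. The only difference falls before entry.
- A reader might infer that an interim efficacy comparison of 50 patients is compromised, since imbalance is larger there. Statistical methods gives that look the purpose of checking technical compliance, fatigue and drop-out. It states no efficacy comparison, and at 50 patients the blocks give exactly 25 and 25.

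**Conclusion.** The point holds in a limited form. The sentence on similarity claims more than a single block list can provide and should be corrected whichever way it was meant. Leaving index disease out of the named tests costs some precision. It does not bias the comparison or raise the false-positive rate, so a reader should not conclude that the planned result would be invalid.

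The size is modest: about an 18% chance (14% with 30% stroke) of a 10-point or larger gap in stroke share at 100 per arm, a shift of 0.05 to 0.15 point against a 1-point target when the gap is 10 points, and a power gain of roughly 0.5 to 4 percentage points. The probabilities rest on the assumed mix. The shift and the gain rest on the assumed gap in MMAS change, and the gain also on an SD of 2. If disease does not predict change, or baseline MMAS already captures its effect, the gain shrinks towards zero. The power figures concern MMAS only; no gain was calculated for TOFHLA.

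**What to change.** 1. **Assignment of interventions.** Replace the similarity claim with a statement that blocking keeps the numbers per arm similar as recruitment proceeds.
2. **Statistical methods.** Replace the unadjusted tests with prespecified regression models for MMAS and TOFHLA, containing treatment arm, index disease (stroke or CAD) and the baseline score, for all randomized patients as allocated. State whether TOFHLA is modelled as a score or as a category. Define index disease from what was recorded before randomization, with a fixed rule for patients who have both diagnoses. The rule must also work for those found through the hospital database and screened by telephone.
3. **Optional.** If enough patients remain to be randomized, the CTU could keep separate block lists by recruiting clinic.

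**Cost.** Items 1 and 2 need no extra patients, visits or data. The real cost is that regression models replace simple two-group tests, for a modest gain. They should be fixed before outcome data are seen by arm. As protocol changes they go through the ethics committee approval and registry reporting that the article requires under Ethics and human subjects' protection. Item 3 needs the same steps, plus a second set of envelopes and possibly one more incomplete block. In a trial already under way, that is harder to justify than the covariate.
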